### Handling of missing data

Because of the 25-week follow-up, efforts will be made to minimize the number of participants lost to follow-up by developing good rapport, making the participant feel comfortable with the research staff and having regular correspondence between assessments. To maintain contact and continued willingness for study participation at each visit participants will provide their current address and phone number and e-mail address as well as contact information for at least two individuals who live outside of their household yet are likely to know their whereabouts. Contact information and contact history will be entered into an electronic database allowing regular review and update.

Although every attempt will be made to avoid missing outcome data, missing data is anticipated with any longitudinal study. The missing data can be defined as intermittent or dropout. The reason for missing data will also be recorded and fully examined to confirm this assumption and to minimize this occurrence in any future confirmatory trials. Where appropriate, non-negligible missing data will be imputed using regression methods.

### Data analysis

The primary goal of this pilot study is to assess the safety and feasibility of delivering DBS to the CnF in PD patients with refractory FOG and thus will only involve 4 subjects. We believe this number of subjects will provide adequate data on safety and feasibility for a larger study. However, assessment of trend toward efficacy will be performed for the secondary outcomes. One-way ANOVA will be used to compare percent improvement in gait velocity for the four different DBS configurations (L CnF off/R CnF off, L CnF off/R CnF on, L CnF on/R CnF off, L CnF on/R CnF on) at each clinic visit, with the Tukey Honest Significant Difference post hoc test to compare configurations. The same test will be used to compare changes in EMG amplitude between the four DBS configurations at the final gait assessment at the study’s conclusion. One-way ANOVA with repeated measures will be used to compare changes in the UPDRS III, FOG Questionnaire, PDQ-39, and PDQL over the multiple time points of the study.

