**Fig. 1 Fig1:**
[figure not shown]
Three-dimensional anatomy of the human MLR and expected side effects of DBS. Reconstructions were made using Lead-DBS and available MNI-space subcortical atlases [44]. A separate CnF (cyan) NIfTI object was created in relation to the PPN (dark purple) based on Olszewski and Baxter’s Atlas [45]. **A** Sagittal projection (5 mm lateral to midline) of the CnF (cyan) and PPN (dark purple) with overlay of active contacts from PPN DBS patients with poor (red), good (green), best (blue), and unevaluated (yellow) gait outcomes from Goetz et al. [43]. **B** Diagonal 3D view with right ML and STT absent to visualize the MLR, projected on to a transverse slice of the brain at the level of the pons. **C** Chart lists nearby structures, their relation to the CnF, and expected side effects of stimulation. CnF Cuneiform nucleus, CTT central tegmental tract, dSCP decussation of superior cerebellar peduncle, LC locus coeruleus, ML medial lemniscus, PPN Pedunculopontine nucleus, RN red nucleus, STT spinothalamic tract. Adapted from Fig. 2 of [46] with permission

Thus, this pilot study is designed to test the safety, feasibility, and preliminary efficacy of CnF DBS in alleviating FOG. Through this and future larger scale studies, we ultimately aim to explore the hypothesis that the CnF represents the neuroanatomic basis of the MLR and that suboptimal targeting may have played a role in the equivocal results of prior PPN DBS studies. We hope to confirm the findings in Goetz et al. [43], which suggest that minute changes in DBS target location in this area have significant impacts on clinical outcome and determine if CnF DBS may be a viable therapy for FOG and other gait dysfunctions.

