**Fig. 2 Fig2:**
[figure not shown]
Flow chart of study outline

Suitable eligible patients will be screened for study participation and begin the consenting process, where the study objectives and the risks and benefits of participating are explained to them. Informed consent forms for the study will be filled out by subjects to confirm enrollment and they will undergo a baseline assessment, including a thorough neurological and neuropsychiatric examination, as well as standardized subjective and objective gait assessments. The Columbia Suicide Severity Rating Scale is included during screening given the known risk of suicidality with DBS for PD [51]. After enrolment and baseline evaluation, subjects will be consented for surgery prior to bilateral implantation of DBS electrodes in the CnF, with a post-operative CT scan to localize final electrode positions. For ethical reasons, all subjects will receive active stimulation beginning at 2 weeks post-implantation and will undergo repeated gait assessments in the clinic at 2-, 6-, 12-, and 24-weeks post implantation (Table 1). Gait assessment tests will be performed on medication, with DBS on and off, and assessors will be blinded to whether the DBS is on or off to minimize the risk of bias. A more detailed kinematics and EMG gait assessment, using the Nexus system (Vicon Motion Systems Ltd) will take place at study onset and conclusion. At study conclusion, subjects will decide whether they want to continue with stimulation or discontinue stimulation; in both cases, they will continue to receive their usual standard care and follow up with their neurologist.

**Table 1 Tab1:** Detailed study schedule

Assessment	Visit 1	Visit 2	Visit 3	Visit 4	Visit 5	Visit 6	Visit 7	Visit 8	Visit 9
	Screen	Baseline assessment	Surgical screening	Surgery	2-week F/U	6-week F/U	12-week F/U	24-week F/U	25-week F/U
**Screening ICF**	X								
**Pre-op work up**^*^ **(CBC, CMP, β-hCG, INR/PTT/PT, U/A, EKG, CXR)**	X		X						
**Neuropsychiatric evaluation (including MDRS and BDI)**	X	X	X		X	X	X	X	
**Columbia Suicide Severity Rating Scale**	X	X	X		X	X	X	X	
**Gait assessment**	X	X			X	X	X	X	
**MDS-UPDRS**	X	X			X	X	X	X	
**FOG Questionnaire**		X			X	X	X	X	
**Timed Up and Go test**		X			X	X	X	X	
**Velocity test**		X			X	X	X	X	
**Variability test**		X			X	X	X	X	
**PDQ-39**		X	X		X	X	X	X	
**PDQL**		X	X		X	X	X	X	
**Brief pain history and NPSI**		X	X		X	X	X	X	
**Surgical ICF**			X						
**MRI**			X						
**Device implantation**				X					

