### Kinematic and EMG evaluation of gait

Lower-limb gait kinematics and EMG will be evaluated with and without DBS in study subjects (*n* = 4). Subjects will be fitted with fifteen reflective markers that will be tracked at 100 Hz with a 10-camera Nexus system (Vicon Motion Systems Ltd) attached bilaterally to the first and fifth distal phalange of the foot, lateral malleolus, calcaneus, lateral femoral epicondyle, anterior superior iliac spine, and the mid-shank and mid-thigh. A reflective marker will also be placed on the lower back region overlying the sacrum. EMG surface electrodes will be placed over the tibialis anterior (TA) as well as the lateral gastrocnemius (LG). Subjects will be asked to walk along a 25-foot path at a constant, regular walking pace both without and then with optimal DBS configuration settings (CnF L on/CnF R on), DBS OFF (CnF L off/CnF R off), DBS RIGHT Only (CnF L off/CnF R on), and DBS LEFT only (CnF L on/CnF R off) repeating each condition twice. Kinematic and EMG signals will be recorded during each trial while the subjects walk for 25 ft. and averaged for each test condition.

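### The efficacy trend rests on at least nine omnibus tests with no control across visits or outcomes, and velocity with and without DBS is tested by a four-group ANOVA that ignores that the same four patients supply every configuration

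*Protocol article*

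**What the plan says.** The Background and rationale (closing paragraph, after Fig. 1) sets the aim: "this pilot study is designed to test the safety, feasibility, and preliminary efficacy of CnF DBS in alleviating FOG". Data analysis makes safety and feasibility the primary goal, says that the study "thus will only involve 4 subjects", and then adds that "assessment of trend toward efficacy will be performed for the secondary outcomes". It does not define a trend.

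The efficacy tests in Data analysis are:

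- **Gait velocity.** "One-way ANOVA will be used to compare percent improvement in gait velocity for the four different DBS configurations" (both off, right only, left only, both on), "at each clinic visit, with the Tukey Honest Significant Difference post hoc test to compare configurations". Study design and overview says patients "will undergo repeated gait assessments in the clinic at 2-, 6-, 12-, and 24-weeks post implantation", so there are four post-implant visits.
- **EMG.** "The same test will be used to compare changes in EMG amplitude between the four DBS configurations at the final gait assessment".
- **Scales.** One repeated-measures ANOVA over time for each of UPDRS III, FOGQ, PDQ-39 and PDQL.

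Two other places describe velocity and the clinic tests as a two-state matter. Secondary outcomes lists the percent change in velocity with and without CnF DBS. Study design and overview has the clinic gait tests done with DBS on and off. The four configurations are described under Kinematic and EMG evaluation of gait.

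**The concern.** There are two linked problems.

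First, several formal tests feed one loosely worded reading, the trend toward efficacy. Tukey's procedure covers the six pairs within one visit. Nothing stated covers the four visits together, or velocity together with EMG and the scales. If velocity separates at week 6 but not at week 24, or one questionnaire moves and the others do not, the text does not say how the efficacy reading follows.

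Second, the velocity test does not match its outcome or the design. The outcome is stimulation on against stimulation off. The test is a four-group omnibus in which on against off is one of six pairs. Ordinary one-way ANOVA also treats the four configurations as independent groups, although each patient contributes to all four. Differences between patients then go into the error term, when they would cancel in a within-patient comparison.

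The Abstract says the pilot is intended to support larger trials of this target. The stake is how far a favourable signal from four patients can be trusted, and how precisely the on/off effect on velocity is estimated.

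**Working it through.** **Plan's own figure.** There is none to reproduce. The article states no alpha, power, effect size or family-wise rate. I assume 0.05 per test.

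**Count of tests.** Velocity at weeks 2, 6, 12 and 24 gives 4, EMG gives 1 and the scales give 4. The total is 9. It is larger if the two recorded muscles, tibialis anterior and lateral gastrocnemius, are tested separately.

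**Chance of at least one p < 0.05 with no effect**

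- Independent tests: 1 − 0.95^9 = 0.370.
- Fully dependent tests: 0.05.
- Null simulation of the nine tests in 4 patients (40,000 runs; scales over 5 time points):

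| Setting | Any p < 0.05 |
|---|---|
| As written, within-patient and between-outcome correlations 0 and 0 | 0.37 |
| As written, 0.5 and 0.5 | 0.21 |
| As written, 0.8 and 0.8 | about 0.13 |
| As written, 0.8 and 0.95 | 0.09 |
| As written, 0 and 0, scale scores serially correlated (0.7), no sphericity correction | 0.43 |
| Velocity and EMG tested within patient, between-outcome correlation 0 to 0.8 | 0.37 to 0.25 |
| Four scales alone, no serial correlation, between-outcome correlation 0 to 0.8 | 0.19 to 0.13 |

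The range is 9% to 43%, or roughly 10% to 40%.

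**Direction.** An omnibus F test rejects for worsening as readily as for benefit. Take favourable to mean that the test is significant and both-on beats both-off, or the last visit is better than baseline. By symmetry each test then has a null rate of 0.025, and nine independent tests give 1 − 0.975^9 = 0.204, against 0.370 for either direction. Requiring the both-on/both-off Tukey pair itself to be significant makes the rate smaller still.

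**Size of the velocity test as written.** With the same 4 patients in all four configurations, a nominal 0.05 one-way ANOVA rejects with probability 0.022, 0.011, 0.0045 and 0.0007 at within-patient correlation 0.3, 0.5, 0.7 and 0.9. It is conservative, so it would also tend to miss a real effect.

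**Precision of the on/off contrast.** Critical values are 2.97 for Tukey (4 groups, 12 df), 2.18 for a single contrast on 12 df, and 3.18 for a paired contrast in 4 patients (3 df). Let r be the within-patient correlation, in units of the between-patient SD. The paired difference has SD √(2(1 − r)), and the expected sample SD from 4 values is 0.921 times the true SD. The mean 95% half-width is therefore 3.18 × 0.921 × √(2(1 − r)) / 2 = 1.46 × √(2(1 − r)).

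| r | Paired difference | One-way ANOVA with Tukey (simulated) |
|---|---|---|
| 0.5 | 1.46 × 1.000, about 1.47 when simulated | 2.03 |
| 0.8 | 1.46 × 0.632 = 0.93 | 1.99 |

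The ratios are 1.47/2.03 = 0.72 and 0.93/1.99 = 0.47. At r = 0 the paired value is 1.46 × 1.414 = 2.07, so there is no gain without within-patient correlation.

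**The case against.** The case against is substantial, and much of it stands.

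- **No claim depends on error control.** Efficacy is a secondary trend assessment, with no threshold, success criterion or go/no-go rule. The Discussion names the small sample and the lack of controls as limitations, and Data Availability commits to dissemination whatever the outcome. A reader might infer that any single positive test may be declared the efficacy trend, but the article nowhere says so. This stands and keeps the severity low.
- **Multiplicity rules may sit in a full protocol or analysis plan that is not shown.** This is fair, and their absence alone would be no finding. The article does, however, fix the tests, the four-level factor, the repetition at each visit and the Tukey step. The mismatch with the on/off outcome lies in those stated choices.
- **On/off is one of the Tukey pairs.** True, so the comparison is delivered, and Tukey does control the pairs within a visit. A reader might count those pairs as a further uncontrolled layer, but they are not. What remains is that the pair is estimated with an error term that ignores the pairing.
- **Time points are not all open.** EMG is fixed at study conclusion, falls run from baseline to the final session, and UPDRS III is relative to the pre-operative baseline. A blanket statement that no time point is named would be wrong.
- **The gain from the fix can be overstated.** Setting 2.97 against 2.18 suggests a 36% wider interval (2.97/2.18 = 1.36), but the paired contrast has a critical value of 3.18. Any gain comes from removing between-patient variation, not from a smaller multiplier.
- **Making velocity the lead is a preference.** The stated target is freezing of gait, and FOGQ comes first among the secondary outcomes. This stands.

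**Conclusion.** The point holds at low severity. The article plans at least nine omnibus tests of efficacy with no stated control across visits or outcomes. It analyses a within-patient on/off outcome with an independent-groups ANOVA over four configurations. At an assumed 0.05 per test, the chance of some significant result in either direction under no effect is roughly 10% to 40%, and about half that or less for a favourable one.

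That range depends on assumed correlations and an assumed alpha. It is not a property stated in the plan, and a reader should not take a narrower band, or the 37% for independent tests, as the trial's error rate. The velocity and EMG tests as written may add few false positives because they are conservative. Even then, the four scales alone give 0.13 to 0.19 in the simulations without serial correlation.

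The firmer part is the choice of method for velocity. If within-patient correlation is 0.5 to 0.8, the paired interval is on average 0.72 to 0.47 times as wide as the Tukey interval. None of this touches the safety and feasibility aims.

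**What to change.** In Data analysis:

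1. Replace the one-way ANOVA with Tukey comparisons for velocity by the within-patient difference, both sides on minus both sides off, at one visit named in advance (for example week 24). Give a 95% confidence interval and all four individual values.
2. State that the other visits, the unilateral configurations, EMG, UPDRS III, FOGQ, PDQ-39 and PDQL are exploratory. Report them as individual values and within-patient estimates with intervals.
3. State that no claim of efficacy or significance rests on the exploratory results.

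If one outcome is to lead the efficacy reading, the sponsor should choose it in advance. Velocity and FOGQ are both defensible.

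The cost is two or three sentences, with no new data, visits or patients. The exploratory comparisons lose formal significance statements.

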## Methods/design

### Study design and overview

This study is a prospective, non-randomized, single-arm, open-label, pilot clinical trial designed to evaluate the safety and feasibility of delivering DBS to the CnF to alleviate freezing of gait in PD patients with severe, levodopa-resistant gait freezing. This study was approved by the University of Miami Human Subject Research Office (UM HSRO) and the US Food and Drug Administration with an Investigational Device Exemption as a phase I trial. The trial is registered in ClinicalTrials.gov: (NCT04218526). The study outline is shown in Fig. 2.

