### Participants

We are actively screening and recruiting patients for this study from the Movement Disorders Clinic at the University of Miami Hospital. As this is a pilot study, we plan to enroll 4 patients with PD with levodopa-resistant FOG. A movement disorder neurologist will assess the eligibility of a patient based on the inclusion and exclusion criteria are detailed below.

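### Gait velocity and EMG across the four DBS configurations are assigned an unpaired one-way ANOVA, although the same four patients supply every configuration

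*Protocol article*

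**What the plan says.** All statements are in the protocol article.

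- Study design and overview: "This study is a prospective, non-randomized, single-arm, open-label, pilot clinical trial". Participants: "we plan to enroll 4 patients with PD with levodopa-resistant FOG". All are implanted bilaterally.
- Kinematic and EMG evaluation of gait: "Lower-limb gait kinematics and EMG will be evaluated with and without DBS in study subjects". The section gives their number as 4 and has each of them walk with both sides on, both off, right only and left only. Each condition is done twice and averaged.
- Data analysis, velocity: "One-way ANOVA will be used to compare percent improvement in gait velocity for the four different DBS configurations". The settings compared are the same four, the comparison is planned for every clinic visit, and pairwise differences are to be tested by Tukey's method.
- Data analysis, EMG: "The same test will be used to compare changes in EMG amplitude between the four DBS configurations". This refers to the end-of-study session.
- Data analysis, scales over time: "One-way ANOVA with repeated measures will be used to compare changes in the UPDRS III, FOG Questionnaire, PDQ-39, and PDQL". Here the repeated factor is the study visit.

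No patient term, block or paired method is given for the configuration comparison. Secondary outcomes lists percent change in gait velocity with and without stimulation. Neither section says which measurement is the denominator of the percent improvement.

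**The concern.** A one-way ANOVA across configurations treats the 16 values as four independent groups of four people. In fact they are four people, each measured four times. Stable differences between patients, and any noise a patient's values share through a common denominator, stay in the error term. They cancel from the comparison between configurations.

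The wording is hard to read as shorthand, because the same paragraph names the repeated-measures form for the scales over time. An analyst who follows the text would use the unpaired form for velocity and EMG.

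The on/off contrast within a patient is the main source of information in a four-patient study. These comparisons are meant to show whether there is a trend toward efficacy that would support a larger trial. The stated test could report no trend when all four patients improve in the same direction. Its error variance would also be the wrong one to carry into planning the next study.

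**Working it through.** **Is there a figure to reproduce?** No. The article gives no alpha, standard deviation, correlation or effect size, and the sample size of 4 is not derived from a formula.

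**Inputs from the article.** Patients n = 4; configurations k = 4; same patients in each; outcome is percent improvement in velocity.

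**Assumed inputs.** Alpha 0.05; mean velocity 0.8 m/s; between-patient SD 0.16; within-patient SD 0.08; true effects 0, 0.08, 0.08 and 0.20 m/s for off/off, the two unilateral settings and both on. The intraclass correlation is 0.16² / (0.16² + 0.08²) = 0.0256 / 0.0320 = 0.8.

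**Step 1: degrees of freedom and cut-offs.**

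| | As written | With a patient term |
|---|---|---|
| Error df | k(n − 1) = 12 | (k − 1)(n − 1) = 9 |
| F critical (3, df) | 3.49 | 3.86 |
| Tukey q (4, df) | 4.20 | 4.41 |

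The patient term costs 3 error df, so the cut-offs rise slightly. The gain comes from the smaller error variance.

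**Step 2: error variance on the percent scale, first-order approximation.** Let s² be the variance of one walk relative to the patient's own level.

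- *Reference is the pre-operative baseline.* Each value carries its own noise (s²) plus the noise of the shared baseline (s²). The one-way error is 2s². The baseline noise is common to a patient's four values, so the within-patient error is s². Tukey width ratio = √2 × 4.20 / 4.41 = 1.35.
- *Reference is the patient's own off walk.* Off/off is 0% for every patient, with variance 0. The other three configurations each have variance 2s². The one-way error is (0 + 3 × 2s²) / 4 = 1.5s². Under no effect, the expected mean square between configurations is only s². Tukey width ratio = √1.5 × 4.20 / 4.41 = 1.17.

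**Step 3: simulation.** 100,000 trials of 4 patients × 4 configurations under the assumed values, each analysed both ways. The pre-operative walk has the same within-patient SD as the others. Trials with a velocity at or below 0.15 m/s were set aside (about 0.2% or fewer).

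| Reference for percent improvement | Power, one-way | Power, repeated measures | Null rejection, one-way | Null rejection, repeated measures | Tukey width ratio (median) |
|---|---|---|---|---|---|
| Pre-operative baseline | 29% | 63% | 1.0% | 4.6% | about 1.3 |
| Own off walk | 42% | 61–62% | 3.0–3.1% | 4.6% | about 1.15–1.2 |

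**Step 4: range.** Between-patient SD of 0.08 to 0.24 (intraclass correlation 0.5 to 0.9), other values unchanged:

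- Pre-operative baseline: one-way power 31% to 26%, against 66% to 59%.
- Own off walk: one-way power 45% to 38%, against 65% to 57%.
- The width ratios hardly move, because the percent metric already removes most of the stable differences between patients.

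(At the top of this range, 3% to 5% of trials were set aside.)

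**Step 5: a check that does not depend on velocity.** For any measure with correlation ρ among a patient's four values, one-way null rejection is 5.0% at ρ = 0, 1.1% at 0.5 and 0.2% at 0.8. Repeated measures stays at about 5.0%. The baseline-referenced percent has ρ of about s² / 2s² = 0.5, which agrees with the 1.0% in Step 3. EMG amplitude has the same structure, but the article does not support a separate figure for it.

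**The case against.** The strongest objection is about importance. The comparison is a secondary look for a trend. The primary goal is safety and feasibility, with the safety analysis descriptive. No stopping rule, sample size or go/no-go decision rests on this F test, and the error is conservative. All of this stands and sets the severity at moderate. It does not make an unpaired test right for paired data.

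A second objection is that percent improvement already removes most differences between patients. That is largely true, and it is why the loss is smaller than raw velocity would suggest. It is not a full remedy: the shared denominator leaves the four values correlated, and one-way power stays well below repeated measures under either reference.

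A third is that the repeated-measures gain assumes equal correlation between configurations, which four patients cannot verify. That is a fair caution about the exact figures. The one-way test, however, assumes no correlation at all.

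A reader might infer more than the article supports:

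- *That the intervals are two to three times too wide, with power near 11%.* Those values arise for raw velocity (ratios 2.1 and 3.0 at intraclass correlations 0.8 and 0.9). The planned outcome is percent improvement.
- *That the off/off group certainly has zero variance.* This follows only if the reference is the DBS-off walk, which the article does not state.
- *That blinded efficacy data are at stake.* Assessor blinding is described for on/off gait tests in the study overview. The section describing the four-configuration walks states none, and the Discussion says complete double blinding may be impossible.

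**Conclusion.** The concern holds at moderate severity. The stated test for velocity and EMG across configurations is the independent-groups one-way ANOVA with Tukey (3 and 12 df), and the data are paired within four patients.

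The direction of the error needs only positive within-patient correlation: too large an error term, a conservative test, and a risk of missing a consistent trend. A reader might infer that the mistake could produce a spurious efficacy signal. Under positive correlation it does the opposite, with null rejection of about 1% or 3% against a nominal 5%.

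The size depends on assumed velocities, effects, alpha and equal correlation. Under those, power is roughly 29% instead of 63% (pre-operative reference) or 42% instead of 61% (off-walk reference). If the off walk is the reference, the zero-variance off/off group also breaks the equal-variance assumption of the one-way ANOVA and of Tukey's test. The safety and feasibility endpoints, and the repeated-measures analysis of the scales over time, are not affected.

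**What to change.** In Data analysis, replace the one-way ANOVA for velocity and EMG with wording such as:

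> Gait velocity and EMG amplitude will be compared across the four DBS configurations by repeated-measures ANOVA, or a mixed model with patient as a random effect (3 and 9 degrees of freedom). Pairwise comparisons, Tukey-adjusted, will use the within-patient error. All four patients' values under each configuration will be shown.

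Also state the reference for percent improvement:

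- If it is the pre-operative baseline, the percent values can be analysed as above.
- If it is the DBS-off walk, analyse log velocity with DBS-off kept as a measured level, and back-transform the contrasts to percent change. This keeps the percent-change outcome and avoids a group fixed at zero.

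The cost is a few sentences in the analysis section. No new data, visits or patients are needed, and the change can be made before the data are analysed.

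### The four stimulation settings form a within-patient left-by-right 2x2, but the plan compares them as four unordered groups, so no contrast uses all four cells to estimate each side's effect or the interaction

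*Protocol article*

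**What the plan says.** The Data analysis section of the protocol article fixes the method for gait velocity: "One-way ANOVA will be used to compare percent improvement in gait velocity for the four different DBS configurations". It lists them as "L CnF off/R CnF off, L CnF off/R CnF on, L CnF on/R CnF off, L CnF on/R CnF on", to be compared at each clinic visit, "with the Tukey Honest Significant Difference post hoc test to compare configurations". For the final assessment it adds: "The same test will be used to compare changes in EMG amplitude between the four DBS configurations at the final gait assessment".

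The section on kinematic and EMG evaluation has each subject walk with both sides on, both off, and under "DBS RIGHT Only (CnF L off/CnF R on), and DBS LEFT only (CnF L on/CnF R off"). Each condition is walked twice and averaged, so every patient supplies one value per cell.

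The repeated-measures form is named only for the rating scale and questionnaires: "One-way ANOVA with repeated measures will be used to compare changes in the UPDRS III, FOG Questionnaire, PDQ-39, and PDQL". The study "thus will only involve 4 subjects", and these secondary analyses are described as looking for a trend toward efficacy.

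**The concern.** The listed settings are the complete crossing of two on/off factors, left and right, within the same patients. One-way ANOVA with all pairs ignores both features.

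- **Crossing.** A pair such as left-only versus off uses two of the four cells and carries a penalty for six comparisons. A left main effect uses all four cells.
- **Interaction.** Whether two leads together give more or less than the sum of each alone is a difference of differences. None of the six pairs estimates it.
- **Patient.** The plain one-way form leaves differences between patients in the error term, although the same section uses repeated measures for other outcomes.

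The pilot is meant to inform larger trials, and whether one side accounts for the benefit bears on their design. With 4 patients there are only 16 patient-by-setting values per analysis, so how they are combined matters.

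**Working it through.** The document gives no SD, effect size, alpha or power for this analysis, so there is no planned figure to reproduce.

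**Inputs.** From the document: 4 patients, 4 cells, one averaged value per patient and cell, Tukey over 6 pairs. Assumed: two-sided 5%, common residual SD s, and patient as a block, which gives (4 − 1) × (4 − 1) = 9 error df.

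**Half-widths of 95% intervals, 9 df**

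| Quantity | Formula | Result |
|---|---|---|
| One Tukey pair | q(0.95; 4, 9) × s/√4 = 4.415 × s/2 | 2.21s |
| One pair, unadjusted | 2.262 × s × √(2/4) | 1.60s |
| Left (or right) main effect, unadjusted | 2.262 × s/√4 | 1.13s |
| Same, Bonferroni for 3 contrasts | 2.933 × s/√4 | 1.47s |
| Interaction (difference of differences), unadjusted | 2.262 × s × √(4/4) | 2.26s |
| Same, Bonferroni for 3 contrasts | 2.933 × s | 2.93s |

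**Ratios.** 2.21/1.13 = 1.95. This splits into √2 = 1.41 from using one pair instead of averaging two, and 2.21/1.60 = 1.38 from Tukey's multiplicity control. At comparable family-wise control the ratio is 2.21/1.47 = 1.5. With 12 df, the one-way ANOVA as written, the corresponding ratios are 1.93 and 1.51.

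**Chance of detection if each side truly adds 1.5s, additively** (an illustration, not a figure from the document):

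- Tukey, left-only versus off: 23%. Counting either of the two pairs that isolate the left side: 38%.
- Factorial left effect: 76% unadjusted, 55% with Bonferroni for three.
- Omnibus F test: cell means 0, 1.5s, 1.5s, 3s give noncentrality 4 × (1.5² + 0 + 0 + 1.5²) = 18 and power 82%.
- Tukey, both-on versus both-off (difference 3s): 84%.
- An interaction of 1.5s, unadjusted: 27%.

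**Blocking.** If the one-way test is run literally, without the patient, its error also contains between-patient variance. Compared with the blocked, unadjusted main effect, its Tukey interval is wider by a factor of 1.9, 2.6 or 3.7 for assumed within-patient correlations of 0, 0.5 or 0.75.

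**Without the common-SD assumption.** If each main effect uses its own 3-df error, the unadjusted half-width is 3.182 × s/2 = 1.59s and the ratio falls to 2.21/1.59 = 1.39. With Bonferroni for three it is 4.857 × s/2 = 2.43s, and the advantage is gone.

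**The case against.** Four arguments deserve weight.

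1. **The plan would still find something.** A reader might infer that it is likely to report no difference between configurations when both sides work. The illustration does not support that: the omnibus test and the both-on versus off pair each have more than 80% power. What is lost is attribution to each side.

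2. **Doubling is not like for like.** A reader might say that the error bars roughly double. That sets a family-wise interval against an unadjusted one. Ignoring the crossing alone costs 1.41, and the comparable figure is about 1.5.

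3. **The factorial model is no cure for the interaction.** A four-level factor and a 2x2 span the same 3 df. The interaction half-width of 2.26s is no better than the Tukey pair. A main effect of 1.5s arises both when each side alone does nothing and the two together give 3s, and when either side alone already gives 3s. This stands, so the interaction must be shown. Both-on versus left-only and both-on versus right-only also bear directly on bilateral leads, so deleting every pair would be a loss.

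4. **Side coding.** A reader might infer that opposite responsive sides cancel in a left/right analysis. The document has no data on a responsive side and states no left-versus-right hypothesis, and its inclusion criteria select predominantly axial symptoms. Any cancellation would affect only the left-minus-right difference (each side's mean effect would be diluted), and a 2x2 coded left/right would share it.

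The analysis is also secondary and no decision rule rests on it. An unseen analysis plan might add contrasts, but the article does not leave the method open: it names the test and the post hoc procedure.

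**Conclusion.** The concern holds in limited form. The document prescribes an unordered four-group comparison for what is a complete within-patient 2x2, and names no estimate of either side's effect across all four cells or of the interaction. With 4 patients and 9 error df, the interval for one side's effect is about 1.5 times as wide as it need be at comparable error control, and 1.95 times against an unadjusted contrast.

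These sizes rest on a common residual SD and on patient blocking, which the velocity and EMG sentences do not state. Reading a main effect as one side's effect also requires little interaction, which 4 patients can barely check. A further condition concerns scale. The secondary outcome is percent change in velocity with and without stimulation. If both-off at the same session is the reference, that cell is zero for every patient, and the common-SD assumption fails in the one-way and the factorial model alike.

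The practical effect is weak attribution by side in an exploratory analysis. The safety and feasibility conclusions are untouched.

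**What to change.** In the Data analysis section, for velocity and EMG wherever all four configurations are measured:

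- Replace the one-way ANOVA with a within-patient 2x2 model (patient as block; left, right and left-by-right terms). Report the three estimates with intervals and say whether these are adjusted. The 1.47s figure applies to a family of these three contrasts.
- Report both-on minus both-off as the overall effect. Keep both-on versus left-only and both-on versus right-only as named comparisons in place of the full set of six Tukey pairs.
- Show each patient's four values.
- Analyse velocity on a scale where both-off is not zero by construction, for example velocity itself, and give percent change descriptively.
- If wanted, recode the unilateral settings by the more affected side as a sensitivity display only.

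The cost is analysis wording, with no new data or visits. The downside is that each main effect averages over the state of the other side, so the imprecise interaction estimate must always stand beside it.
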